# Is casting of displaced paediatric distal forearm fractures non-inferior to reduction under general anaesthesia? Study protocol for a pragmatic, randomized, controlled non-inferiority multicentre trial (the casting trial)

**DOI:** 10.1186/s13063-024-08253-z

**Published:** 2024-06-27

**Keywords:** Forearm injuries, Wrist injuries, Salter-Harris fractures, Closed fracture reduction, Child, Bone remodelling

## Abstract

**Background:**

Treatment of displaced distal forearm fractures in children has traditionally been closed reduction and pin fixation, although they might heal and remodel without surgery with no functional impairment. No randomized controlled trials have been published comparing the patient-reported functional outcome following non-surgical or surgical treatment of displaced paediatric distal forearm fractures.

**Methods:**

A multicentre non-inferiority randomized controlled trial. Children aged 4–10 years with a displaced distal forearm fracture will be offered inclusion, if the on-duty orthopaedic surgeon finds indication for surgical intervention. They will be allocated equally to non-surgical treatment (intervention) or surgical treatment of surgeon’s choice (comparator). Follow-up will be 4 weeks and 3, 6, and 12 months. The primary outcome is the between-group difference in 12 months QuickDASH score. We will need a sample of 40 patients to show a 15-point difference with 80% power.

**Discussion:**

The results of this trial may change our understanding of the healing potential of paediatric distal forearm fractures. If non-inferiority of non-surgical treatment is shown, the results may contribute to a reduction in future surgeries on children, who in turn can be treated without the risks and psychological burdens associated with surgery.

**Trial registration:**

www.clinicaltrials.gov (ID: NCT05736068). Date of registry: 17 February 2023.

**Supplementary Information:**

The online version contains supplementary material available at 10.1186/s13063-024-08253-z.

## Background and rationale

Paediatric distal forearm fractures (DFFs) are common and account for 25–30% of all fractures in children [1, 2]. In Denmark, the incidence among 4–10-year-old children is approximately 900/100,000 persons, corresponding to 3500 injuries per year [3], of which nearly half are treated surgically [4]. The most common treatment of displaced paediatric DFFs is currently closed reduction under general anaesthesia with or without pin fixation (or in rare cases plate and screw fixation), followed by immobilization in a cast [5]. However, surgery may have detrimental effects, such as fear, anxiety, and complications related to surgery. Eliminating these effects are desirable for the individual child and family. Children’s bones, and in particular the metaphysis and physis, have a unique ability to heal and remodel throughout the growth period [6], making a non-surgical approach a possible alternative. If more distal forearm fractures could be treated non-surgically in the future, the surgical capacity and allocated surgeons could be prioritized to patients of higher needs. As these fractures would be carried out in an outpatient setting, there will be no need for hospitalizations, benefitting both the individual patient and the health care system. In addition, from a socioeconomic perspective, re-prioritizing the use of healthcare resources could result in considerable financial savings [7–9].

Numerous studies, including small cohort studies, randomized controlled trials (RCTs), and case series, have found pin fixation advantageous in achieving anatomic reduction and avoiding re-displacement [10–16]. However, it is unknown whether patient-reported outcomes benefit from anatomic reduction and stabilization, as most studies use only radiographic or objective measures such as range of motion (ROM). During the last 20 years, only four studies have been published, investigating non-surgical treatment of displaced DFFs in prepubertal children. These include one Finish case–control study [17], one British prospective cohort study [18], and two retrospective case series from Finland and Hawaii, respectively [8, 19]. These studies do however agree that displaced DFFs might heal well without reduction and that most fractures will remodel almost to the anatomical position with no functional impairment within a year or two.

There are currently two other ongoing RCTs comparing non-surgical treatment to surgical treatment. One is a large study in England, the CRAFFT study [20], randomizing 750 children nationwide with displaced distal forearm fractures to non-surgical or surgical treatment comparable to the interventions in this trial. The other RCT is conducted in Finland [21], randomizing 60 children with overriding distal forearm fractures to surgical treatment or non-surgical treatment, where finger trap traction is used to align only angulation but not dorsal displacement or shortening. To the best of our knowledge, no RCTs have been published yet, and none of the existing studies report outcomes from the patient’s perspective.

### Objective

The objective of this trial is to compare patient-reported outcome measures (PROMs) assessing function, quality of life, and pain following non-surgical versus surgical treatment of displaced DFFs in 4–10-year-old children.

### Trial design

A pragmatic, randomized, controlled non-inferiority multicentre trial with two parallel groups allocated 1:1 by block randomization. Primary outcome is patient-reported function after 1 year.

## Methods

This trial protocol was written according to the SPIRIT guidelines (Additional file 1) [22].

### Study setting

The trial will be conducted at orthopaedic surgery departments at four Danish university hospitals in Køge, Aarhus, Aalborg, and Odense.

### Eligibility criteria

For definition of the metaphysis, we will use the AO classification for children, as illustrated in Fig. 1 [23].

**Fig. 1 Fig1:**
[figure not shown]
The metaphysis defined by the AO square with its sides being the same lengths as the width of radius and ulna at the level of the radius growth plate

### Inclusion criteria

Children 4–10 years of age with open physesDisplaced fractures in the distal metaphyseal radius with or without concomitant ulna fracture (S52.5 (distal radius) and S52.6 (distal radius and ulna)), including extra-articular physeal fractures (Salter-Harris (SH) I–II)◦ Overriding fractures or◦ Angulated fractures of 20–40°The on-duty surgeon finds reduction under anaesthesia with or without fixation indicated

### Exclusion criteria

Open fracturesNerve or vascular affectionIntraarticular fractures including SH III–VUlnar physeal fracturesPolytraumaConcomitant ipsilateral or contralateral upper extremity fractures (except distal ulna fracture)Pathologic fracturesThe injury is > 7 days oldOther conditions that may affect bone healing

### Informed consent

A child presenting with a displaced DFF is screened for eligibility. If the eligibility criteria are fulfilled, the surgeon will briefly introduce the project and ask the parents/guardians to meet in the outpatient clinic the following day. Here, the local investigator will provide both oral and written information including trial participant’s rights and a consent form (Additional file 6). The information will be adapted to the child’s ability to understand the project and its importance for them. After a reflection period, the parents/guardians will be asked for written consent.

## Interventions

A cast will be applied in the emergency room as standard procedure. Children will be randomly allocated 1:1 to:Non-surgical treatment (intervention): No reduction. Cast optimization if necessarySurgical treatment (comparator): Reduction under general anaesthesia with or without pin fixation of surgeons’ choice followed by cast immobilization

The cast will be removed after 4 weeks if radiological signs of healing (callus formation or bone bridges). The casting will be prolonged another 2 weeks if uncertainty of healing. If the initial cast was an above elbow cast, it will be changed to a below elbow cast at this point.

### Discontinuation

Compartment syndrome and carpal tunnel syndrome has been described in relation to distal forearm fractures. However, the evidence-base is very limited and is primarily based on case reports in fractures after reduction [24, 25]. Thus, as these complications appear after surgery, we expect a lower incidence in the non-surgical group.

### Adherence to intervention

It is not possible to cross-over from surgical to non-surgical treatment. Although the opposite is possible, efforts will be made to avoid cross-overs, and changing from non-surgical to surgical treatment will be considered a drop-out. Patients dropping out will be scheduled for usual care, i.e. surgery as long as the fracture has not healed, and preferably within 5 days from injury for physeal fractures and within 10 days for metaphyseal fractures.

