### Secondary outcome measures

Secondary outcomes will include the following:QuickDASH (3 and 6 months)Health-related quality of life (HRQoL) using EQ-5D-Y [38, 39] (3, 6, and 12 months), andPain using Wong-Baker Faces Pain Scale (WBS) [40] (3, 6, and 12 months)

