### Sample size

We defined a non-inferiority margin as NIM = MCID = 15 QuickDASH points. Thereby, we will only reject the null-hypothesis, if the between-group difference is *both* more than NIM *and* clinically relevant. With an SD = 15 and type I error rate of 2.5%, 16 patients per group (32 in total) would be required for 80% power that the lower limit of a 95% two-sided confidence interval (CI) would be above the non-inferiority limit [44]. Allowing for 20% dropouts, the total sample size required is 40 patients (20 in each group).

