### Primary outcome analysis

The primary endpoints will be reported as mean QuickDASH scores on a continuous scale between 0 and 100 and will be analysed by the per-protocol (PP) population and repeated, for sensitivity reasons, for the intention-to-treat (ITT) population. Non-inferiority will be concluded only if both PP and ITT analyses show non-inferiority.

The between-group difference in mean QuickDASH score by 12 months will be compared using linear mixed effects models (LMM).

Non-inferiority will be concluded if the lower end of the 95% CI is above the NIM of 15 QuickDASH points.

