### Handling of missing data

LMM will be used to deal with missing values, assuming the dropout mechanism is missing at random (MAR). We distinguish between item-wise missing (more than one, but not all, answers in a questionnaire are missing) and case-wise missing (all answers in a questionnaire are missing). Case-wise missing will be addressed using LMM. Incomplete questionnaires with item-wise missing will be addressed by multiple imputation, if the number of questionnaires excluded due to missing items exceeds 5%.

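### Children who change from casting to surgery are classed as drop-outs, so as written they may be missing from both PP and ITT, and requiring both would not guard against their selective loss

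*Protocol article*

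**What the plan says.** Under Adherence to intervention, the protocol article treats a move from surgery to casting as impossible. For the opposite move it says that "changing from non-surgical to surgical treatment will be considered a drop-out". Children who drop out are then booked for usual care, meaning surgery while the fracture is unhealed, "preferably within 5 days from injury for physeal fractures and within 10 days for metaphyseal fractures".

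The QuickDASH assessments named in the outcome sections are the secondary ones, "QuickDASH (3 and 6 months", and the primary one at 12 months. The schedule in Table 1 is not reproduced in the text available.

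Under Primary outcome analysis, PP is the main analysis and ITT is repeated as a sensitivity analysis, with the rule: "Non-inferiority will be concluded only if both PP and ITT analyses show non-inferiority". Membership of the two populations is not spelled out.

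The same term appears in two other places. Under Sample size, the total is raised from 32 to 40 to allow for 20% dropouts. Under Handling of missing data: "LMM will be used to deal with missing values, assuming the dropout mechanism is missing at random (MAR".

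**The concern.** Requiring both PP and ITT protects a non-inferiority conclusion only if the two analyses treat departures from the allocated treatment differently. PP leaves those children out; ITT should keep them in the arm to which they were randomised. If a change to surgery makes the child a drop-out in the sense used in the sample-size and missing-data sections, there is no 12-month score for either analysis.

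The loss can occur in the casting arm only. It may also be related to outcome, since treatment is unblinded and every enrolled child had a surgeon who judged reduction under anaesthesia to be indicated. At stake is what the trial estimates: the effect of a policy of casting, or the result of casting among children who stayed with it.

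**Working it through.** **Inputs.** From Sample size: "We defined a non-inferiority margin as NIM = MCID = 15 QuickDASH points"; "With an SD = 15 and type I error rate of 2.5"% (one-sided); "16 patients per group (32 in total) would be required for 80% power"; 20% dropouts; 40 in total, 20 per group. QuickDASH runs from 0 to 100, higher being worse. I take the difference as casting minus surgery, so non-inferiority means an upper 95% limit below 15. The number of children who change treatment and their 12-month scores are not in the article. They are assumptions below.

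**The plan's own figure.** n per group = 2 × 15² × (1.960 + 0.842)² / 15² = 15.7, rounded up to 16. Total 32, and 32 / (1 − 0.20) = 40. The stated size reproduces. Power at 16 per group is 80.7% by the normal approximation and 78.1% by the t distribution. Dividing by 0.80 treats a drop-out as supplying no outcome.

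**The timing.**
- Surgery after a change: preferably within 5 or 10 days of injury.
- First follow-up QuickDASH named: 3 months.
- Primary QuickDASH: 12 months.

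A child who stops supplying data at the change has no post-treatment QuickDASH. The mixed model then has no follow-up outcome from that child to use under MAR, whether the analysis is labelled PP or ITT.

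**Precision.** With 16 per arm, SE = 15 × √(2/16) = 5.30 and t(30) = 2.042, so the half-width is 10.8. Non-inferiority needs an observed difference below 15 − 10.8 = 4.2 points. A shift of about 3 points therefore matters.

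**Direction A: the lost children would have scored worse.** Let a share c of the casting arm be lost, each scoring D points worse than the other casting children. Leaving them out flatters the casting mean by c × D. With the true all-randomised difference at 15, the apparent difference is 15 − cD.

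| c | D | Shift | Apparent difference | False non-inferiority (t, 16 per arm) |
|---|---|---|---|---|
| 0 | – | 0 | 15 | 2.5% |
| 15% | 20 | 3 | 12 | 7.9% |
| 20% | 30 | 6 | 9 | 19.4% |

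**Direction B: the lost children would have scored like the surgical arm.** If the all-randomised difference is 15 and a share c has difference 0, the rest have difference 15 / (1 − c).

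| c | Apparent difference | False non-inferiority |
|---|---|---|
| 15% | 15 / 0.85 = 17.6 | 0.7% |
| 20% | 15 / 0.80 = 18.8 | 0.4% |

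**Simulation check.** 100,000 trials per setting, 20 per arm, SD 15, true difference 15, and 1 to 6 casting children changing treatment.
- Four lost from both analyses: 2.5% if they score like other casting children, 5.8% if 10 points worse, 8.3% if 15 worse, 11.8% if 20 worse.
- The same children followed and kept in ITT, with both analyses required: about 1.5-2.3% across all settings from 1 to 6 children and 0 to 20 points.

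**The case against.** The strongest reply is that the article never says QuickDASH collection ends when treatment changes. Its retention section excludes children who fail to attend after two phone reminders and keeps data up to withdrawal; a change of treatment is neither. Adverse events are to be grouped by treatment received, which suggests that these children remain under observation. One can read the sentence as dropping out of the allocated treatment, hence out of PP but not out of ITT. Table 1 is not shown, so a QuickDASH at baseline or 4 weeks cannot be excluded, and the 5- and 10-day limits are preferences.

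This stands as far as it goes. A reader might infer that ITT certainly loses the same children as PP and that the double requirement is empty. The article does not establish that. ITT may also still use 3- and 6-month scores from children lost later. What remains is that the word chosen is the one the article uses for lost outcome data, and nothing says these children are followed.

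A reader might also infer that the loss must favour casting because these are failed casts. The article gives no reason for a change, and its Discussion accepts that casting may seem counter-intuitive to families and surgeons, so preference is equally possible. Direction A is also demanding. At c = 15% and D = 20 the remaining casting children are 12 points worse than the surgical arm and those who changed are 32 worse; at c = 20% and D = 30 the figures are 9 and 39. Yet those who changed received surgery.

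Finally, a reader might infer a serious loss of power. Falling to 13 against 16 evaluable children lowers power from 78.1% to 73.3%, but needs 7 of the 20 casting children lost. Three losses fit within the allowance of four per arm, which may already be meant to cover treatment changes.

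**Conclusion.** The point holds as a defect in a stated rule, with its effect uncertain. The article classes a one-directional treatment change as a drop-out, uses that term elsewhere for missing outcomes, and then relies on PP and ITT both succeeding. Taken literally, early changes would probably be missing from both analyses, and for those children the double requirement would give no protection.

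Neither size nor sign of the bias can be fixed from the article. On assumed inputs (SD 15, 16 per arm, true deficit at the margin), the false non-inferiority rate ranges from about 0.4% to 19%, against a nominal 2.5%. It stays at 2.5% if the lost children score like the other casting children. The case for changing the text rests on not leaving this open: a 12-month score that was never collected cannot be recovered at analysis.

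**What to change.** Replace the sentence under Adherence to intervention with wording such as: A change of allocated treatment is a protocol deviation, not a drop-out. The child stays in follow-up, completes every QuickDASH to 12 months, is analysed in the randomised arm for ITT and is excluded from PP.

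Reserve drop-out for withdrawn consent or lost outcome data, in line with the sample-size and missing-data sections. Report the number changing treatment in each arm.

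The cost is wording in the protocol and analysis plan, plus questionnaires for what may be a handful of children through the links already in use. N stays at 40, and no rule on clinical care changes.

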### Protocol violation

Loss to follow-upHealth conditions precluding participation

The trial will be discontinued if unexpected and serious complications arise, and all participants will be notified and offered standard treatment.

### Insurance

Insurance of the trial is covered by The Danish Patients Compensation Fund.

## Outcomes

Patients will be followed up by 4 weeks and 3, 6, and 12 months. The surgeon may schedule the patient for an additional post-operative 1 week control if preferred. If needed, we will offer long-term follow-up of patients beyond the scope of this trial.

### Primary outcome measure

The primary outcome will be the PROM, Quick Disabilities of Arm, Shoulder and Hand (QuickDASH) [26], at 12 months. This 11-item questionnaire is a shortened version of the 30-item Disabilities of the Arm, Shoulder and Hand (DASH) [27]. The DASH was designed to help report the disability experienced by adults with upper-limb disorders covering different activities of daily living, and also monitoring changes over time.

The QuickDASH has, like the DASH, two four-item optional modules, work and sports/performing artists, which are scored separately. The QuickDASH and the DASH have comparable psychometric properties [28].

The patient rates each item (with help by parents if the patient is too young to self-report) according to the perceived degree of severity using a 5-point Likert scale. The overall score is transformed to a score between 0 and 100 (0 = no disability, 100 = maximum disability).

Although the QuickDASH was developed on adults, it has been used in several studies on children with different upper extremity fractures. Unfortunately, these studies report only total QuickDASH scores (mean (standard deviation (SD))) and *p*-values but do not take into account the clinical relevance of the differences [29–33].

We have identified four studies using anchor-based approach to determine the minimal clinically important difference (MCID) in adults [34–37]. Mintken et al. [37] reported an MCID of 8 on 101 adults with shoulder pain. Sorensen et al. [35] reported an MCID of 14 on 48 adults with non-operatively treated atraumatic hand and forearm conditions. Franchignoni et al. [34] reported an MCID of 15.9 on 266 adults with upper-limb musculoskeletal disorders, referred to inpatient and outpatient physiotherapy. In a similar population, Polson et al. [36] reported an MCID of 19 on 35 adults with musculoskeletal conditions to the upper extremity, referred to physiotherapy. We derive an MCID of 15 from the reported MCIDs, and since no MCID is reported in children’s cohorts, we assume it to be roughly comparable to adults.

To estimate an SD for the QuickDASH, we identified SDs in studies on children with upper extremity fractures. Quatman-Yates et al. [29] reported an SD of 19.3 in 149 children aged 8–12 years referred for outpatient rehabilitation following upper extremity injury. Ernat et al. [33] assessed 752 supracondylar fractures in 2–13-year-old children and the relationship between fracture classification and QuickDASH after 3 months (range 1–13 months). They reported SDs of 11.6 in Gartland II and 16.4 in Gartland III. Eguia et al. [32] did a cross-sectional survey 4.4 years (range 2–10 years) post-operatively on 508 children aged 3–8 years with a supracondylar humerus fracture treated with crossed or lateral pinning. They reported SDs of 5.8 and 8.8, respectively. Roper et al. [31] did a cross-sectional study 5 years post-injury on 30 children < 18 years old with closed or open Monteggia fractures and reported SDs of 6.1 and 8.8, respectively. Overall, there seems to be a tendency for the SD to decrease over time. Assuming these populations are roughly comparable to those of our study, the SD should be somewhere between 11.6 and 16.4 by 3 months (with a range up to approximately 1 year) and 5.8 and 8.8 by 4.4 years. From these assumptions, we conservatively estimate the SD to be 15, since our primary outcome at 12 months is closer to 3 months than 4.4 years.

### Secondary outcome measures

Secondary outcomes will include the following:QuickDASH (3 and 6 months)Health-related quality of life (HRQoL) using EQ-5D-Y [38, 39] (3, 6, and 12 months), andPain using Wong-Baker Faces Pain Scale (WBS) [40] (3, 6, and 12 months)

#### EQ-5D-Y

The EQ-5D-Y is a child-friendly version of the EuroQol EQ-5D generic measure of HRQoL. It consists of two parts: the first part (the descriptive system) assesses health in five dimensions (mobility; looking after myself; doing usual activities; having pain or discomfort; feeling worried, sad or unhappy), each of which has three levels of response. This part of the EQ-5D-Y questionnaire provides a description of the respondent’s health by generating a health state profile. The second part of the questionnaire, the EQ VAS, consists of a visual analogue scale (VAS) on which the respondent rates their perceived health from 0 (the worst imaginable health) to 100 (the best imaginable health). We define an MCID of 10 EQ VAS points and SD = 20, based on a study including 3–6-year-old children, either healthy or with acute or chronic illness [41].

